### Interventions

#### Overview

Regardless of the group (STR or FPT), each session will consist of a warm-up activity (5-10 minutes), main exercise activity (30-40 minutes), and cool-down activity (5-10 minutes) following the guidelines of a multicomponent exercise program, Vivifrail [46]. Exercise intensity will be controlled based on the Rating of Perceived Exertion (RPE) [47] on the Borg scale [48] and heart rate measured with a smartwatch [49] before, during, and after each exercise session according to the guidelines of the American College of Sports Medicine [47]. The warm-up and cool-down activities will include stretching and walking in place (9≤RPE≤10 and 40<55% maximum heart rate (HRmax), while the main exercise activity will consist of strength, resistance exercise, cardiovascular exercises, and balance exercises (to prevent falls) performed using dumbbells, color-coded resistance bands (Thera-Band; Hygienic Corp) [50] and a chair (11<RPE≤15 and 55<70 HRmax).

To ensure safety and compliance, exercise training will be supervised by a health professional (physical therapist) who has been appropriately trained (research support staff). This health professional will provide one-on-one instructions to each participant according to the target RPE and HRmax (measured with a smartwatch) for each session. All participants will interact with the same health professionals.

Specifically, in each session, the resistance exercise will be carried out through squats, dumbbells, or chair-based exercises using a color band (as an example of the exercise progression: yellow [level 1] band during weeks 1-4, red [level 2] band during weeks 5-8, and green [level 3] band during weeks 9-12). This routine will focus on the main muscle groups in the shoulders, arms, thighs, hips, and calves, including 3 or 4 sets with 8 to 15 repetitions per set [51]. The balance exercise will include 2-legged standing, tandem standing, single-legged standing, semitandem standing, tandem walking, turning in a circle around the chair, and exercises such as toe-standing exercises, which will focus on postural muscle groups. Cardiovascular exercise will consist of walking at a pace at which you can maintain a continuous conversation, but it costs a little effort. Walking duration may increase (8-15 minutes) as the sessions go by. The total exercise duration progressively increased from 40 to 60 minutes over the course of the intervention period. Previous international studies that analyze STR programs have used similar exercise protocols [19,52].

To increase adherence to the interventions and avoid eliminating participants, WhatsApp groups will be created, and messages will be sent to remind participants to participate in the exercise sessions.

#### STR Program (STR Group)

During the exercise session, the participants turn on the tablet PC, watch the instructor perform the exercise, and follow the instructor’s movements. For the instructor to observe the correct movements of the participants, the resistance and balance exercises are performed in the frontal and sagittal planes. During each session, a technical staff member will supervise up to 4 or 5 participants who are exercising remotely at home using a real-time videoconferencing app (Zoom Communications). The videoconference session will be shown on a television screen located in an older adult care center. Once the technical staff has been assigned to participants, their supervision will not be interchangeable. Participants will be able to see and interact with both the health care professionals and other participants. The older adults, from their homes, will complete 1-hour sessions twice a week for 12 weeks (Figure 2).

#### FPT Program (FPT Group)

The exercise sessions will take place in a center for older adults, lasting 40 to 60 minutes, twice a week for 12 weeks, and will include a combination of cardiovascular, balance, strength, flexibility, and gait exercises (Figure 2).

### Outcome Measures

#### Overview

Physical fitness, functional status, and quality of life will be examined before and after the interventions. All measurements will be performed by a health professional (technical staff will be trained), blinded to the group allocation scheme, which will guarantee an unbiased procedure. In addition, all measurements will be conducted in a face-to-face setting and obtained individually in an environment with optimal conditions of privacy, temperature, and humidity, such as an older care center collaborating with the project. Data will be recorded on standardized forms and entered into a secure access database that contains quality control checks (eg, range checks and notifications for missing data). The main outcome for this trial will be lower body strength (assessed in the 30-second chair stand test) and cardiorespiratory fitness (evaluated using the 2-minute step test). Secondary outcomes included upper limb strength, dynamic balance, static balance, number of daily steps, functional status, and quality of life.

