### Objectives

In this context, this study aims to analyze whether the effectiveness of an STR program is better than a face-to-face physical therapy (FPT) program in the primary outcomes (lower body strength and cardiorespiratory fitness) and secondary outcomes (upper limb strength, dynamic balance, static balance, number of steps, functional status, and quality of life) in older adults who are frail. We hypothesize that (1) both STR and FPT programs improve primary (lower body strength and cardiorespiratory fitness) and secondary outcomes (upper limb strength, dynamic balance, static balance, number of steps, functional status, and quality of life) in older adults who are frail and (2) STR produces equal or greater improvements compared to face-to-face programs in these outcomes.

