### Power Calculation

The sample size was calculated a priori using G*Power 3.1.9.7. A total of 52 participants in total are required (26 in each group), considering Cronbach α=.05, 1-β=.8, and effect size=0.8 (lower limb strength based on the results of a previous study) [19]. Considering the possibility of abandonment, 6 participants were added (N=58; n=29 in each group; Figure 1 [42]).

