### Statistical Analysis

Missing data will be handled by intention-to-treat analysis (multiple imputation method) [67]. The description will be made as measures of central tendency and dispersion (continuous variables) and as percentages (categorical variables). Using the Shapiro-Wilk test, the normality of the data will be verified, and a two-step approach for transforming will be applied to the nonnormal variables [68]. Homoscedasticity will be analyzed using Levene test. A 2-way repeated measures ANOVA will be used to determine the effects of interventions. The effects of the model are the group (experimental group vs control group), the time points (before and after test), and their interaction over time (time × group). The Bonferroni post hoc test will be applied to identify statistically significant comparisons. The *t* test effect size will be determined using Cohen *d* (<0.2 insignificant; ≥0.2 and ≤0.49 small; ≥0.5 and ≤0.79 moderate; ≥0.8 large) [69]. All analyses will be performed using SPSS (version 26; IBM Corp), with a significance level of *P*<.05, and GraphPad Prism (version 8).

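### Two unordered primary outcomes are each tested at P<.05 with no success rule: error reaches up to 9.75% if either one counts, and the stated 80% power is lost if both must succeed

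*Protocol article*

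**What the plan says.** - Objectives lists "primary outcomes (lower body strength and cardiorespiratory fitness") jointly. The Overview under Outcome Measures repeats the pair: "The main outcome for this trial will be lower body strength (assessed in the 30-second chair stand test) and cardiorespiratory fitness". Neither outcome is ranked above the other.
- The second hypothesis in Objectives expects the telerehabilitation (STR) arm to do as well as or better than face-to-face therapy (FPT). It covers primary and secondary outcomes together.
- Statistical Analysis gives one test for every outcome: "A 2-way repeated measures ANOVA will be used to determine the effects of interventions". It gives one threshold for all analyses: "with a significance level of *P*<.05".
- The only adjustment named there is a follow-up to the ANOVA: "The Bonferroni post hoc test will be applied to identify statistically significant comparisons".
- Power Calculation covers one outcome, "effect size=0.8 (lower limb strength based on the results of a previous study"). No effect size is given for cardiorespiratory fitness.

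**The concern.** With two primary outcomes, the reader has to know what counts as a positive trial. The article leaves two readings open, and each costs something it states. If a significant result on either outcome is enough, the chance of a false positive is above 5%. If both are needed, the chance of success is below the 80% used for sizing.

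The Bonferroni sentence looks like an answer but is not one. It follows the ANOVA of a single outcome. Group has two levels and time has two, so each factor offers only one pairwise comparison. Even if the correction were spread over all four group-by-time cells, it would stay within one outcome.

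What is at stake is that the success rule could be chosen after the results are known: significance on strength alone, or on fitness alone, could be reported as a positive primary result.

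**Working it through.** **Inputs.** Two primary outcomes (Objectives; Outcome Measures, Overview). Significance level .05 per test (Statistical Analysis). For sizing, "considering Cronbach α=.05, 1-β=.8, and effect size=0.8"; the word Cronbach is read here as a slip for the significance level. Required size: "A total of 52 participants in total are required (26 in each group"), raised to 58 (29 per group) for dropout. The correlation between the two primary tests is not given, so a range is assumed.

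**1. The plan's own figure.** With two groups and two time points, the time × group test is equivalent to a two-sample t test on change scores. For d=0.8, two-sided .05, n per group, the noncentrality is d·√(n/2) on 2n−2 degrees of freedom. The smallest n with power of at least 80% is 26, with power 80.7%, which matches the stated 26 per group and 52 in total. A one-sided .05 gives 21 per group and does not match. The trial was therefore sized with the full two-sided .05 on lower-limb strength.

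**2. Either outcome counts.** Independent tests: 1 − 0.95² = 0.0975. For correlated tests, the probability that at least one |z| exceeds 1.96 comes from the bivariate normal distribution. The last column counts only false results in favour of STR, that is, at least one z above 1.96; for a single outcome this is 2.5%.

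| Assumed correlation | At least one false positive, two-sided | At least one false result favouring STR |
|---|---|---|
| 0 | 9.75% | 4.9% |
| 0.5 | 9.1% | 4.5% |
| 0.7 | 8.3% | 4.2% |

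The two-sided figure is still 7.0% at a correlation of 0.9 and stays above 5% at any correlation below 1.

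**3. Both must succeed.** The error is at most 5%. For power, d=0.8 is assumed for fitness as well. Marginal power is 80.7% with 26 per arm and 84.9% with 29. Independent outcomes: 0.807² = 0.65 and 0.849² = 0.72. At a correlation of 0.7, the bivariate normal gives 0.72 and 0.78.

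| Per arm | Power for strength alone | Power for both, correlation 0 to 0.7 |
|---|---|---|
| 26 | 80.7% | 65–72% |
| 29 | 84.9% | 72–78% |

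**4. Splitting alpha, for comparison.** At .025 per outcome, the familywise error is 1 − 0.975² = 4.9% under independence and never above 5%. Power at d=0.8 is 71.6% with 26 per arm and 76.9% with 29. Reaching 80% takes 31 per arm, 62 in total before dropout.

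**The case against.** **The tempting stronger reading.** A reader might infer that the trial's false positive rate simply is nearly 10%. The article does not support that. The figure needs an either-outcome success rule, which is stated nowhere, and independent tests. Rising from a chair and stepping in place both depend on the legs, so positive correlation is plausible and lowers it. The figure also counts errors in both directions, whereas Objectives asks whether STR is better; false results favouring STR stay just under 5%, though that is still nearly twice the 2.5% for one outcome.

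**The hypothesis could be read as requiring both outcomes.** It speaks of the outcomes together, and under a both-must-succeed rule the error is controlled. But it covers the secondary outcomes in the same sentence and is worded as an expectation, not a decision rule. On that reading the 80% power fails instead.

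**A success rule may sit in an analysis plan that is not shown.** That is fair, and silence alone would not be a finding. But the article does fix a flat threshold for all analyses, says where Bonferroni acts, and sizes the trial on one outcome at the full .05. A later split of alpha would not fit the published sizing.

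**Counting every test.** Adding the secondary outcomes gives larger figures: 1 − 0.95⁸ = 34% with one test for each of the eight listed outcomes, or 1 − 0.95¹⁵ = 54% if the eight SF-36 dimensions are tested separately. Both assume independence. The article does not say that each dimension will be tested, and it claims no confirmatory status for secondary outcomes, so the conclusion does not rest on either figure.

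**The fixed sequence is not the only remedy.** This stands. Requiring both outcomes or splitting alpha would also control error, at the power shown above. The hypothesis also allows for equal results; if the arms are equal, a superiority test on strength will usually close the gate before fitness is reached.

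**Conclusion.** The point holds in conditional form. As written, error across the two primary outcomes is not controlled, because they are unordered, each is tested at .05, and the Bonferroni step works within an outcome. Under an either-outcome rule, the two-sided familywise error is up to 9.75%, and 9.1% to 8.3% at assumed correlations of 0.5 to 0.7. Under a both-outcome rule the error is at most 5%, and the cost moves to power: 65–72% with 26 per arm, or 72–78% with 29 per arm before any information is lost to missing data. The power figures assume d=0.8 on fitness, for which the article gives no value. The correlation changes the size of the problem, not its existence.

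**What to change.** Add to Statistical Analysis, before outcome data are analysed, a fixed sequence: test the time × group effect on lower-limb strength at two-sided .05, and test cardiorespiratory fitness at two-sided .05 only if strength is significant. Strength goes first because the trial was sized on it. State that secondary outcomes will be reported with 95% confidence intervals and without confirmatory claims.

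Before the sequence can be applied, the strength measure must be reconciled. The Overview under Outcome Measures names a 30-second chair stand test, while Lower Limb Strength under Primary Outcomes describes a timed 5-repetition sit-to-stand.

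The cost is one paragraph and no extra participants. Familywise error is held at 5%, and the power stated for strength is unchanged. The downside is that fitness supports no confirmatory claim if strength is not significant. If the investigators prefer to require both outcomes or to split alpha, they should say so and restate the power or sample size; a split needs 62 participants against 52 before dropout.

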#### Primary Outcomes

##### Lower Limb Strength

This will be measured using a 5-repetition sit-to-stand test. The older adults will be asked to stand up and sit down, as quickly as possible, 5 times from a chair without armrests located against a wall. The time will be measured from the beginning of the movement until the older adult manages to stand up for the fifth repetition. The older adult’s arms should be crossed over the chest during the test. The time will be recorded in seconds and tenths of a second [53,54].

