### Recruitment of Participants

All individuals aged ≥60 years belonging to CIAM Los Angeles will be invited to participate. Research support staff will conduct recruitment in person or by telephone. To be eligible for participation, individuals must meet the following inclusion criteria: (1) both sexes aged ≥60 years, (2) older adults from the CIAM, (3) older adults diagnosed with frailty according to the modified Fried phenotype scale [5], (4) ability to stand up and walk ≥10 m without assistive devices, (5) Abbreviated Mini-Mental State Examination >13 points [45], and (6) no medical contraindication for physical exercise. In addition, older adults must have a smartphone or tablet and an internet connection at home. Computer or internet literacy is not required as an eligibility criterion. Exclusion criteria include older adults with fractures, recent acute myocardial infarction, associated cardiovascular pathology, severe acute respiratory failure, high blood pressure, uncontrolled diabetes mellitus, limitations following instructions, as well as individuals participating in another exercise program during the project (Figure 1).

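### The timed 5-repetition sit-to-stand has no value for a participant who cannot reach the fifth stand, and the only stated rule for absent values, multiple imputation, would assign a time that is too fast

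*Protocol article*

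**What the plan says.** All references are to the protocol article.

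- **Lower Limb Strength** (Primary Outcomes) names the test: "This will be measured using a 5-repetition sit-to-stand test". Timing has one end point: "The time will be measured from the beginning of the movement until the older adult manages to stand up for the fifth repetition". The participant's "arms should be crossed over the chest during the test", and "The time will be recorded in seconds and tenths of a second". No cap, code or worst score is given for someone who does not get there.
- **Overview** (Outcome Measures) names a different test for the same primary outcome: "lower body strength (assessed in the 30-second chair stand test".
- **Recruitment of Participants** requires frailty on the modified Fried phenotype and, as the functional criterion, "ability to stand up and walk ≥10 m without assistive devices". Five stands without use of the arms are not required, and there is no upper age limit.
- **Statistical Analysis** has one rule for absent values: "Missing data will be handled by intention-to-treat analysis (multiple imputation method"). The imputation model and its assumptions are not described, and the text does not say whether inability counts as missing. The main model is stated as: "A 2-way repeated measures ANOVA will be used to determine the effects of interventions", with group, time and their interaction.

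**The concern.** Inability to finish is a result. It is the worst result that this test can show, and it has been observed. A completion time cannot express it, so on the form it would be a blank. Overview says that the database flags missing data, and the only written instruction for missing data is imputation. An analyst who follows the text literally would therefore impute a time for the weakest participants from the data of those who finished.

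Two comparisons are exposed. The first hypothesis in Objectives is that both programmes improve the outcomes. That rests on within-arm change, which is distorted if more people are unable at one visit than at the other: a participant who loses the ability has the decline hidden, and one who gains it has the gain understated. The second hypothesis is that telerehabilitation does at least as well as face-to-face therapy. If inability differs by arm, the arm difference is pulled towards zero, which makes a reading of equality easier to reach.

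**Working it through.** **The plan's own figure.** Power Calculation gives 52 (26 per arm) for d = 0.8, alpha 0.05 and power 0.80. A two-sided two-sample t-test needs 25.5, so 26 per arm, with power 0.807; adding 6 gives 58. The figure reproduces and this point does not change it.

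**How many could be affected.** The documents give no inability rate. Under assumed overall rates:
- 5%: 0.05 × 58 = 2.9 participants
- 10%: 0.10 × 58 = 5.8
- 20%: 0.20 × 58 = 11.6

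For comparison, the dropout allowance is 6.

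**Simulation set-up (assumptions).** 29 per arm, 1,000 runs per scenario. Latent time is in SD units, and higher is slower. Baseline is fully observed, with baseline to post-test correlation 0.5 or 0.8. One arm is shifted so that the stated share in each arm exceeds a common completion cutoff at post-test. Those above the cutoff are blanked and filled by normal multiple imputation (20 imputations) on baseline and group. The estimate is the between-arm difference in change, which with two visits is the time × group effect.

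**Where imputation places the unable.** Their true mean was 1.75 to 2.17, and the cutoff was 1.28 or 1.64. Their mean imputed value was 0.19 to 0.70 at correlation 0.5 and 0.91 to 1.36 at correlation 0.8. It lay below the cutoff, within the completers' range, in every scenario.

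**Between-arm difference when inability is unequal.** Shrinkage = 1 − (imputed estimate / true difference), from the rounded values shown.

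| Unable, slower vs other arm | Correlation | True | Imputed | Shrinkage |
|---|---|---|---|---|
| 10% vs 5% | 0.5 | 0.36 | 0.29 | 19% |
| 20% vs 10% | 0.5 | 0.44 | 0.30 | 32% |
| 20% vs 5% | 0.5 | 0.80 | 0.61 | 24% |
| 30% vs 10% | 0.5 | 0.76 | 0.51 | 33% |
| 10% vs 5% | 0.8 | 0.36 | 0.33 | 8% |
| 20% vs 10% | 0.8 | 0.44 | 0.37 | 16% |
| 20% vs 5% | 0.8 | 0.80 | 0.69 | 14% |
| 30% vs 10% | 0.8 | 0.76 | 0.61 | 20% |

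**Between-arm difference when inability is equal** (5% or 10% in both arms). The true difference is 0. The estimates were between −0.02 and 0.00, and the rejection rate was 0.05 to 0.06, so there was no bias.

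**Within-arm change in the same equal-rate runs.** Approximate error in each arm's post-test mean = share unable × (true mean − imputed mean of the unable):
- 10%, correlation 0.5: 0.10 × (1.76 − 0.19) = 0.16 SD too fast
- 10%, correlation 0.8: 0.10 × (1.75 − 0.91) = 0.08 SD
- 5%, correlation 0.5: 0.05 × (2.06 − 0.35) = 0.09 SD
- 5%, correlation 0.8: 0.05 × (2.07 − 1.19) = 0.04 SD

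The true change here is zero, so each arm appears to improve by that amount.

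**Power at 30% vs 10%.** At correlation 0.5: imputation 0.45, worst-rank test on post-test alone 0.78, full latent data 0.84. At correlation 0.8: 0.87, 0.77 and 0.99. The post-test-only rank test discards baseline, and that costs it when baseline is a strong predictor.

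**The case against.** The strongest reply is that the article never says inability will be treated as missing. It sends the test procedure to cited sources and refers to standardized forms that are not shown. A code and score for failed attempts could stand there or in the analysis plan. This is fair, and it limits the point. A reader might infer that the plan does give non-completers a completer-like time. The text supports only the conditional: it would, if a blank time is handled under the one rule stated and with a standard model. What remains is that the article itself fixes an outcome that has no value for its weakest participants and offers no other rule.

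Other limits also stand:

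- A reader might infer that the comparison of arms is biased in any event. It is biased only if inability differs by arm. Both arms follow the same exercise programme, and nothing in the article points to a difference.
- The problem does not arise under the 30-second count named in Overview.
- The entry criterion lowers the chance of failure, and no rate is given. No effect in seconds can be derived from the article.
- Timed Up and Go is also a completion time, but it asks for a single stand and a short walk at usual pace, without crossed arms. Entry nearly guarantees that at baseline, so it is at most a minor parallel case.
- Worst-score methods are not always more powerful than imputation, as the correlation 0.8 result shows. That bears on which remedy to choose. The imputed estimates were still shrunken in that setting.

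**Conclusion.** The point holds in conditional form. As Lower Limb Strength defines it, the timed test leaves a foreseeable result without a value, and the only written rule for absent values does not suit that result. If the rule is applied with a missing-at-random model, the unable receive times that are too fast. Under assumed rates of 5% to 30% per arm and correlations of 0.5 and 0.8, a real between-arm difference shrinks by about 8% to 33% when inability is unequal and is unbiased when it is equal. Within-arm change is off by about 0.04 to 0.16 SD when 5% to 10% become unable only at post-test. These sizes illustrate the mechanism and do not forecast this trial. A stronger baseline predictor reduces the error but did not remove it. The sample size is unaffected. The matter merits correction because a rule is cheap to set in advance and hard to defend if chosen after the data are seen.

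**What to change.** 1. Reconcile Overview with Lower Limb Strength on which chair-stand test is the primary outcome.
2. If the 30-second count is kept, zero stands is a valid observed score and no further rule is needed.
3. If the timed test is kept:
   - Add a form field at each visit that separates attempted but unable from not assessed.
   - Score unable as an observed worst result. One form is a worst-rank analysis in which the unable share the worst rank at that visit and the post-test rank is adjusted for the baseline rank. Another is stands per second with unable = 0, checked by a rank-based analysis.
   - Report the number unable by arm and visit.
   - Use multiple imputation only for participants who were not assessed.

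The same field can be added for Timed Up and Go at little extra effort.

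**Cost.** One form field and a few sentences of analysis text, with no change in sample size. Results would be on a rank or rate scale that does not convert directly to a mean time; a zero rate corresponds to no finite time. Zeros also sit far from the other values and strain the normal-theory repeated measures ANOVA, hence the rank-based check. A rank test on the post-test alone should be avoided because it discards baseline. The baseline-adjusted rank analysis was not itself simulated here.
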